### Intervention

A visual depiction of the study flow and planned timeline is provided in Additional file 2. A detailed description of the intervention is provided in Additional file 3. A screenshot of the virtual learning centre and training modules are shown in Additional File 4. A brief summary of the intervention has been described and is visually depicted in Fig. 2. A client (the research participant) will receive a visit in their home from a pair of trained volunteers. The volunteer pair will collect information electronically using a tablet computer which houses a specifically designed Health TAPESTRY software application (TAP-App). Information such as life and health goals, daily life activities, and general health will be collected using structured surveys and unstructured narratives (see Additional file 3). The information gathered will be organized in a report summarizing any alerts, key issues, observations, and goals. This report will be securely sent electronically to an intake team at the clinic. Intake teams may include any combination of healthcare professionals and were put in place to address high-health-need patients including high users of the healthcare system and Health TAPESTRY clients.

**Fig. 2 Fig2:**
[figure not shown]
Health TAPESTRY process. Volunteers visit clients in their home and use the Health TAP-App to collect information. This information is summarized on a Health TAPESTRY report and is uploaded into the person’s electronic medical record to be shared with the intake team at the clinic. Reports are viewed and an action plan is developed which can include community organizations and resources, volunteer follow-up visit, and follow-up in any nature by healthcare team members and the client using their personal health record. The Health TAPESTRY process continues in an iterative fashion until the participant is discharged from the program

Each clinic will decide which healthcare team members should be included in the intake team and define a process that works best within their workflow. The clinic intake teams will review the reports and connect with the appropriate interprofessional healthcare team across the MFHT making sure to include the most responsible family physician. Collectively, a care plan is generated to facilitate how the team, community agencies, and the volunteers can address the client’s goals and health issues. The intervention treatment period will be 6 months.

### Control

The control group will receive the usual care. These individuals will not have volunteer visits or be discussed at an intake meeting. They may or may not have had a previous PHR account. At the conclusion of the 6-month trial, the control group will have the option of receiving the intervention.

### Follow-up

Follow-up for the purposes of research will be according to intention to treat (ITT) and take place throughout implementation (qualitative data collection) at 6 and 12 months (quantitative data collection) in the intervention and control groups. Clinical follow-up during the intervention will be determined by clinical needs.

### Outcomes

Tables 2 and 3 summarize the measures, timing, and data collection method used for the primary and secondary outcomes, in addition to the measures and timing of the implementation processes. The following section gives more detail for clarity and is broken down into two broad sub-sections: client outcome measures and implementation processes. A description of the tracking of adverse events and the economic analysis is also included.

**Table 2 Tab2:** Summary of trial client outcomes and implementation processes

Client outcomes				
Variable/outcome	Hypothesis	Outcome measure	Timing	Methods of analysis^a^
Goal attainment	GAS score will be higher in the intervention arm compared to the control arm at 6-months; proportion of participants who report maintaining or improving in the top priority goal area will be higher in the intervention arm than the control arm at 6-months	Goal attainment scaling score [53] obtained from a structured interview; proportion of participants who report maintaining or improving in their top priority goal area	*T* _6_, *T* _12_	Linear regression for continuous variables; logistical regression for categorical variables
Self-efficacy	*Higher* self-efficacy, quality of life, optimal aging, social support, access, comprehensiveness, patient empowerment, patient-centeredness, and satisfaction of care and *lower* caregiver strain, hospital admissions, and emergency room visits will be reported in the intervention arm compared to the control arm at 6-months	Self-efficacy for managing chronic disease [55]; self-report	*T* _0_, *T* _6_, *T* _12_	
Quality of life		EQ5D-5L [56]; self-report	*T* _0_, *T* _6_, *T* _12_	
Optimal aging		Single-item optimal aging question from the Canadian Longitudinal Study on Aging [57]; self-report	*T* _0_, *T* _6_, *T* _12_	
Social support		DUKE social support index [58]; self-report	*T* _0_, *T* _6_, *T* _12_	
Access		CIHI common indicators; self-report [59]	*T* _0_, *T* _6_, *T* _12_	
Comprehensiveness of care			*T* _0_, *T* _6_, *T* _12_	
Patient empowerment			*T* _0_, *T* _6_, *T* _12_	
Patient-centeredness			*T* _0_, *T* _6_, *T* _12_	
Caregiver strain		4-item Zarit screen [60]; self-report	*T* _0_, *T* _6_, *T* _12_	
Satisfaction with care		Single item, satisfaction rated from 1 to 10; self-report	*T* _0_, *T* _6_, *T* _12_	
Hospitalizations and emergency room visits		EMR abstraction	*T* _0_, *T* _6_, *T* _12_	

Demographic information including age, gender, level of education, marital status, ethnicity, language spoken, and number of medications, falls, adverse events, and economic analysis not included in the above table

*T*
_*0*_ baseline, *T*
_*3*_ 3-month collection, *T*
_*6*_ 6-month collection, *T*
_*12*_ 12-month collection

^a^Analyses will be adjusted for participant gender and MFHT site (McMaster Family Practice or Stonechurch Family Health Centre)

**Table 3 Tab3:** Summary of trial client outcomes and implementation processes

Implementation processes			
Variable/outcome	Outcome measure	Timing	Methods of analysis
Volunteer self-efficacy	3-item self-efficacy rating of communication with client, performance of tasks necessary for home visit (i.e., navigate TAP-App) and handling unexpected issues (0–100 % scale)	Prior to each home visit	Mean differences for the first 3 months of visits compared to the second 3 months of visits
Completeness of TAP-App used by volunteers	Time to complete each module; number of items missed	*T* _6_, *T* _12_	Mean differences where applicable
Client satisfaction with volunteers	Description of experience with volunteer home visits	*T* _3_, *T* _12_	Qualitative descriptive method
Uptake of personal health record by clients	PHR metrics including number of times logged in, features used, number of secure messages sent, issues encountered, and described experience with the personal health record	*T* _0_, *T* _6_, *T* _12_	Mean differences where applicable; content analysis with frequency counts of each category where applicable
Type and extent of healthcare team involvement with client	Chart audit to track actions of healthcare team (type of follow-up, team members involved)	*T* _6_	Content analysis with frequency counts of each category of resource
Quality and extent of healthcare team functioning and organizational readiness for change by health team members	Described in qualitative interviews	*T* _3_, *T* _12_	Qualitative descriptive method
	ORCA [66]		Mean difference between *T* _3_ and *T* _12_
How often and what types of community resources are utilized by clients?	Chart audit to track connections to community resources and programs	*T* _6_	Content analysis with frequency counts of each category of resource
Type and extent of involvement of clients in program	Described in qualitative interviews	*T* _6_	Qualitative descriptive method
Type and extent of involvement of family caregivers in the program	Research session notes; described in qualitative interviews	*T* _6_	Content analysis with frequency counts of each category of resource
What life and health goals are generated by clients?	Structured open-ended questions in research session	*T* _6_, *T* _12_	Thematic analysis of goals based on goal areas
Process of implementation and factors influencing implementation	Described in qualitative interviews	*T* _3_, *T* _12_	Qualitative descriptive method

Demographic information including age, gender, level of education, marital status, ethnicity, language spoken, and number of medications, falls, adverse events, and economic analysis not included in the above table

*T*
_*0*_ baseline, *T*
_*3*_ 3-month collection, *T*
_*6*_ 6-month collection, *T*
_*12*_ 12-month collection

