### Randomization and blinding

While it is recognized that there could be potential contamination between intervention and control groups by the primary care providers who will have participants in both arms, the intervention focuses on identifying a person’s health goals which a salient component to all other actions to take place as part of the intervention. Thus, without the processes in place to receive information about a person’s goals, contamination is unlikely, and so it was felt that clustering at the level of the practice was not necessary.

The randomization process will involve an automated central (allocation concealed) computerized randomization sequence, with the patient as the unit of randomization. Randomization will be stratified by participant gender and MFHT site (McMaster Family Practice or Stonechurch Family Health Centre). Couples will be accepted into the study to encourage study participation and to ensure equitable access to the intervention. Recognizing the potential influence of one member of a couple on the other, both members will be randomized into the same group. One member of the couple will be randomly selected to contribute their data to the main analysis.

Participants, caregivers, and volunteers will not be blinded; however, there will be some masking of groups: participants will not explicitly be told that they are in the initial or delayed group. Physicians and other members of the healthcare team will be not be formally blinded to allocation; however, there will be some masking as they will only know a participant is receiving the intervention once a Health TAPESTRY report is reviewed and may not recognize whether a person has been allocated to the intervention or control group. Data analysts will be blinded to the study group.

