#### Primary outcome

The primary outcome is the mean difference in the goal attainment scale (GAS) score at 6 months over baseline in the intervention arm, compared with the control group [52]. Participants will identify health goals, indicators, and outcomes through structured, prompted discussion. Each participant will rate their progress towards achievement of their goal using a set of five expected outcome levels for each indicator related to that of health goal. Outcome levels identified will be as descriptive, objective, and observable as possible and phrased as relative versus absolute improvements [53]. At 6 months, a GAS score will be calculated for each participant according to conventional methods [52] and used as the primary outcome. The proportion of participants’ self-reporting maintenance or improvement in their top priority goal area will be used as a secondary outcome. Further details about the process for gathering data to create the GAS are provided in Additional file 5.

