The analysis will be blind to study group allocation and will follow ITT principle. Dropouts will not be replaced. Reporting will follow the CONSORT extension for pragmatic randomization trials [66] and non-pharmacological interventions [67]. The baseline characteristics of the practices and patients will be reported by group as mean (standard deviation) or median (first quartile, third quartile) for continuous variables, depending on the distribution, and count (percent) for categorical variables. Multiple imputations will be used to handle missing data to enable ITT analysis. The data will be analyzed using generalized estimating equations—assuming exchangeable correlation structure adjusting for baseline scores, to analyze all outcomes [68]. The results will be reported as estimate of the effect, corresponding 95 % confidence interval and associated *p* values. All *p* values will be reported to three decimal places with those less than 0.001 reported as *p* < 0.001. The criterion for statistical significance will be set a priori at alpha = 0.05 and adjusted using the Bonferroni method for multiple secondary analyses. Analyses will be performed using SAS V9.4 (Cary, NC). There will be a single final analysis at the end of the trial. Subgroup analyses will include examining differences between the following groups: men and women; age less than 80 and 80+ years; those residing alone and residing with others; or those with three or more chronic conditions.

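### The primary GAS model may have no baseline prognostic term: the plan adjusts for a baseline score that Table 2 never schedules and names no other T0 covariate

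*Protocol article*

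**What the plan says.** Two places in the protocol article fix the covariates. Footnote a to Table 2 (Outcomes) reads: "Analyses will be adjusted for participant gender and MFHT site (McMaster Family Practice or Stonechurch Family Health Centre". The Client outcomes part of Data analysis specifies generalized estimating equations, "assuming exchangeable correlation structure adjusting for baseline scores, to analyze all outcomes". Gender and site are also the stratification factors in Randomization and blinding: "Randomization will be stratified by participant gender and MFHT site (McMaster Family Practice or Stonechurch Family Health Centre".

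On whether GAS has a baseline value, the article points both ways:
- Table 2 gives T6 and T12 as the GAS time points. The other client outcomes in that table are listed at T0, T6 and T12.
- Primary outcome says "At 6 months, a GAS score will be calculated for each participant according to conventional methods", yet defines the endpoint thus: "The primary outcome is the mean difference in the goal attainment scale (GAS) score at 6 months over baseline in the intervention arm".
- Power and sample size assumes a baseline GAS of 30 in both groups.

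Other measures are taken at T0, including "Self-efficacy for managing chronic disease [55]; self-report" and "EQ5D-5L [56]; self-report", together with optimal aging and social support. The notes to Table 2 add "age, gender, level of education, marital status, ethnicity, language spoken, and number of medications, falls" without a collection time. None of these is named as a covariate for GAS.

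**The concern.** For most secondary outcomes the baseline-score term has a T0 value to use, and a person's own earlier score is usually the best single predictor of the later one. For GAS, on the Table 2 schedule, that term has nothing to use. The primary comparison would then be adjusted only for the two strata.

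A scored T0 GAS might not help much either. Primary outcome says that the outcome levels are phrased as relative rather than absolute improvement. If everyone starts at or near the same defined level, a starting score carries little information. That is an inference; the article does not say how a T0 score would be distributed.

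At stake is the width of the primary confidence interval. In a randomized comparison with a continuous outcome, a prespecified covariate measured before the intervention reduces residual variance by the share that it explains. The data for several candidates are already being collected.

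**Working it through.** **Inputs.** From Power and sample size: difference 5 GAS points, SD 15, power 80%, type I error 0.05, 286 patients before loss. Equal arms (143 each) and a two-sided test are assumed; a one-sided test would give 224, which does not match. The R² of the T0 measures with 6-month GAS is not in the documents and is assumed over 0 to 0.20.

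**Step 1: reproduce the plan's figure.** Normal approximation: n per arm = 2 × (1.960 + 0.842)² × 15² / 5² = 141.3, so 142 per arm and 284 in all. The t-test version gives 142.25, so 143 per arm and 286 in all. The stated 286 reproduces. It uses the full SD of 15, so it takes no credit for covariates.

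**Step 2: precision without a prognostic term.** SE of the difference = 15 × √(2/143) = 1.774. The standardized effect is 5/1.774 = 2.819, and t-test power is 80.2%.

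**Step 3: precision with covariates.** Residual SD = 15 × √(1 − R²). The SE shrinks by the factor √(1 − R²). The number of unadjusted patients giving the same precision is 286/(1 − R²).

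| Assumed R² | SE factor | 5/SE | Power, 286 analysed | Equivalent N | Extra patients |
|---|---|---|---|---|---|
| 0 | 1.000 | 2.819 | 80.2% | 286 | 0 |
| 0.05 | 0.975 | 2.892 | 82.2% | 301 | 15 |
| 0.10 | 0.949 | 2.971 | 84.2% | 318 | 32 |
| 0.15 | 0.922 | 3.057 | 86.1% | 336 | 50 |
| 0.20 | 0.894 | 3.151 | 88.1% | 358 | 72 |

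The normal approximation gives 80.5%, 82.4%, 84.4%, 86.4% and 88.3%, which is within 0.3 points throughout.

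**Step 4: cost if the covariates predict nothing.** With arm, gender, site and an intercept, 286 − 4 = 282 degrees of freedom remain. Three more covariates cost about 3/282 = 1.1% of variance. The standardized effect becomes 2.819/√1.011 = 2.803, which by the normal approximation takes power from 80.5% to 80.0%. Break-even is where (1 − R²) × 1.011 = 1, an R² of about 0.01. The table does not deduct this cost.

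**Step 5: where a baseline GAS stands.**
- If T0 GAS is not scored, the baseline-score term is empty for the primary outcome, and R² in the table is the contribution of the other T0 measures.
- If it is scored but nearly constant, the result is practically the same.
- If it is scored and varies, it is already a prognostic term, and the other T0 measures add only what they explain beyond it.

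The article does not settle which case applies.

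**The case against.** The strongest reply is that nothing here is invalid. Adjusting for the stratification factors is correct, leaving out further covariates causes no bias, and the sample size delivers its 80% without them. All of that stands.

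A second reply is that covariate selection belongs in the analysis plan or the full protocol. This fails, because the article does state covariates in two places, and one of them may not exist for the primary outcome.

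A third reply concerns prediction. A reader might infer that no listed covariate predicts GAS and that the T0 measures do, so that precision is certainly being given up. The documents do not support that. They report no association between GAS and gender, site or any T0 measure. Goals are individualised and meant to be realistic for each person (Discussion), so the scaling may already absorb differences in starting health. The gain could be close to nil. A baseline GAS may also exist, as the endpoint definition and the assumed baseline of 30 suggest; details of the GAS process are in Additional file 5, which is not at hand.

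A fourth reply is that unbiased adjustment needs covariates taken before the intervention and in the same way in both arms. Number of medications has no stated collection time. Client outcome measures places the chart audit at the end of the study and allows surveys to be given either by volunteers on home visits or through the researchers' software, while controls receive no volunteer visits. This stands and limits which variables may be used.

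**Conclusion.** The point holds in a limited form. The covariates stated for the primary analysis are two strata and a baseline score whose existence the article leaves contradictory. If that score is absent or nearly constant, the primary model has no baseline prognostic term although candidates are collected at T0.

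The consequence is possible lost efficiency. With 286 analysed, power is 80.2% at R² = 0 and would be 88.1% at R² = 0.20. That range is assumed, and it also rests on SD 15, a difference of 5, equal arms and a two-sided 5% test. A reader might go further and conclude that the trial is biased or underpowered by its own figures; neither follows, because the 286 reproduces with no covariate gain.

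**What to change.** 1. State whether a GAS score is taken at T0, and bring Table 2, Primary outcome, Client outcomes and Power and sample size into line with the answer.
2. Prespecify, before unblinding, one primary model: linear regression of 6-month GAS on arm, gender and site, T0 GAS if it is scored, and a short list of covariates measured before the intervention, such as T0 self-efficacy, T0 EQ-5D-5L and age, entered as continuous terms. Include number of medications only if it is recorded at T0 in both arms.
3. Confirm that each chosen covariate is collected at T0 in the same way in both arms.
4. Keep the model with gender and site only as a sensitivity analysis.

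The change is one of wording. It needs no new data provided that step 3 is met. The downside is a few degrees of freedom, about 1% of variance, if the covariates turn out to predict nothing.

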#### Client outcome measures

Data on client demographic and other characteristics, as well as outcome measures, will be gathered using multiple data collection methods including self-report client surveys, clinic EMR, volunteer-administered TAP-App, and research program records. Outcome data measures will be repeated at 6 and 12 months. Client surveys will be programmed into the software administered by the volunteers during home visits or into software (REDCap, Version 6.9.7, Vanderbilt University [49]) used by researchers.

Data abstraction from clinic EMRs will be carried out using a structured, pilot-tested form. Chart audit of each patient examining the number of visits, the clinicians involved, and any referral or consultations internally or externally, as well as any physical measurements such as blood pressure, fasting blood glucose level, and lipids will take place at the end of the study. Data abstraction will occur independently in duplicate until reasonable agreement has occurred (i.e., 0.70), as calculated by Kappa statistic [50, 51]. Administrative data on health services utilization will be acquired from the EMR.

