#### Client outcomes

We propose to test using two analysis sets: ITT set, considering all patients as randomized regardless of whether they received the intervention and a “per protocol” analysis set. A per protocol analysis will include all participants who received the intervention including both members of a couple assigned to the intervention group compared with all participants randomized to the control group including both members of a couple assigned to the control group.

Quantitative data analysis will include descriptive analyses with means and standard deviations calculated for the continuous variables and frequencies calculated for categorical variables. Data will be summarized in tabular or graphical form. The main between-group comparison will take place at 6 months. This point also serves as the control group’s baseline as they move into the intervention arm based on the delayed design. The comparison at 12 months then compares the effect of the intervention after 12 months of participation (original intervention group) versus 6 months of intervention (original control group).

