Interventions and expertise	Experimental intervention-flexibility	TAP-reports reviewed and action plan is developed for that particular person based on their individual self-report information so action plans are all different. There is not a “one size fits all” approach to reports. No specific instructionsgiven to intake teams on process, allowed teams to develop own process and workflow for TAPESTRY; practice was allowed to be different between the two clinics. Never forced clients to use PHR to facilitate connection to healthcare team. At least one home visit by the volunteer was initiated, but no minimum or maximum follow-up visits were enforced in the trial	5
	Experimental intervention-practitioner expertise	MFHT and intake teams made up of different people, intake teams changed throughout the trial, elements of care plan carried out by various MFHT members, regardless of level of expertise	5
	Comparison intervention-flexibility	Control individuals allowed to receive any type of care from any healthcare professional at the clinic. Individuals in the control group do not receive volunteer visits, the TAP-App and are not discussed at the intake team meetings	5
	Comparison intervention-practitioner expertise	Same MFHT members are involved in the care of individuals in the intervention and control groups	5
Follow-up and outcomes	Follow-up intensity	Formal follow-up to collect research outcomes (baseline, 6 and 12 months). No formal volunteer home visit follow-up schedule of clients, no instruction for MFHT of clinic follow-up	4
	Primary trial outcome	Primary out is GAS score, which is subjective, person-centered care outcome and clinically meaningful to client	5
Compliance/adherence	Participant compliance with “prescribed” intervention	No formal strategy to encourage compliance; methods to encourage use of PHR, improve volunteer confidence in role	5
	Practitioner adherence to study protocol	Only subtle strategies to encourage intervention to move forward have left for organic process, but no formal strategy to monitor adherence or encourage adherence; researchers sat in intake team meetings early on to track development of processes, however, have withdrawn researchers have intake teams to lessen influence of initiative	4
	Analysis of primary outcome	Using intention to treat principle, intention to include all experiences in evaluation (good and bad), statistical analysis plan will work under “noise”	5

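### Self-report outcome surveys may be taken by the intervention's own volunteers, a route that up to the 6-month comparison exists in the intervention arm only

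*Protocol article*

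**What the plan says.** Under Client outcome measures, the article says that client characteristics and "outcome measures, will be gathered using multiple data collection methods including self-report client surveys, clinic EMR, volunteer-administered TAP-App, and research program records". It then describes two homes for the surveys: "Client surveys will be programmed into the software administered by the volunteers during home visits or into software" (REDCap) used by researchers. Neither sentence assigns a route by measure, arm or time point.

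The volunteers belong to the intervention. The Intervention section says: "A client (the research participant) will receive a visit in their home from a pair of trained volunteers". They also know the allocation; Randomization and blinding states: "Participants, caregivers, and volunteers will not be blinded; however, there will be some masking of groups".

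Controls lack this route. The Control section says: "These individuals will not have volunteer visits or be discussed at an intake meeting". Table 4 in the Discussion repeats it: "Individuals in the control group do not receive volunteer visits, the TAP-App and are not discussed at the intake team meetings". That holds up to the main analysis: "The main between-group comparison will take place at 6 months". Only afterwards do controls gain access: "At the conclusion of the 6-month trial, the control group will have the option of receiving the intervention".

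**The concern.** Table 2 lists ten self-report survey outcomes: self-efficacy, EQ-5D-5L, optimal aging, social support, access, comprehensiveness, empowerment, patient-centeredness, caregiver strain and satisfaction with care. Several ask the client to judge the care received, or support and confidence that the programme aims to raise. Answers to such questions can depend on who asks. If some intervention clients answer to the volunteers who visit them while every control answers to a researcher, a courtesy or mode shift enters one arm and looks like a treatment effect.

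The planned analysis cannot remove it. Intention to treat, multiple imputation and blinded analysts do not address differential measurement. The stated adjustment terms are gender, site and baseline score. A term for mode would help little, since mode would nearly coincide with arm. EQ-5D-5L also supplies the utilities for the cost-utility analysis, so a shift there would carry into the economic result.

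**Working it through.** **Step 1: which routes exist in each arm.**

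| | Intervention arm, T0 to T6 | Control arm, T0 to T6 |
|---|---|---|
| Volunteer visit with TAP-App | yes (Intervention section) | no (Control section; Table 4) |
| Researcher with REDCap | yes | yes |

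A survey value taken by a volunteer in this period can therefore belong only to the intervention arm. After T6 controls may opt in, so the imbalance at T12 is weaker.

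**Step 2: the plan's own sample size.** Inputs from Power and sample size: difference 5, SD 15, power 80%, alpha 0.05 (taken as two-sided). Per arm, 2 × (1.960 + 0.842)² × (15/5)² = 141.3, so 142 per arm and 284 in total. The t-test version gives 142.2, so 143 per arm and 286 in total, which is the stated figure. The point changes no stated number. I use 142 per arm below; using 143 moves each rate by less than one percentage point.

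**Step 3: illustrative size.** The article gives no mode effect, so the shift d (in SD units) is assumed. Let f be the fraction of the intervention arm surveyed by volunteers. With no true effect, the two-sample t statistic has 282 degrees of freedom and non-centrality f × d × √(142/2) = f × d × 8.43. The false-positive rate is the probability that |t| exceeds 1.968 at alpha 0.05, or 2.829 at alpha 0.005. The second level applies the Bonferroni rule stated under Client outcomes in Data analysis to the ten survey outcomes: 0.05/10 = 0.005. The number of tests is my assumption.

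| Assumed shift | f = 1, alpha 0.05 | f = 1, alpha 0.005 | f = 0.5, alpha 0.05 | f = 0.5, alpha 0.005 |
|---|---|---|---|---|
| 0.1 SD | 13% | 2.5% | 7% | 0.9% |
| 0.2 SD | 39% | 13% | 13% | 2.5% |
| 0.3 SD | 71% | 38% | 24% | 6% |

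This is a plain t-test, not the planned baseline-adjusted model. For f = 0.5 it ignores the small extra variance from mixing modes.

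**Step 4: the same shift on the trial's scales.** With the SDs in Power and sample size and f = 1, 0.2 SD is 0.2 × 2.5 = 0.5 points on self-efficacy, half of the 1.0 target. On EQ-5D-5L it is 0.2 × 0.3 = 0.06, which is 60% of the 0.10 target.

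**The case against.** The strongest reply is that the article never assigns a Table 2 outcome to the volunteers. The source list pools demographics, other characteristics and outcomes. The Intervention section describes the TAP-App as gathering goals, daily activities and general health for the care report. Table 4 separates formal research follow-up at baseline, 6 and 12 months from volunteer visits, which have no follow-up schedule, and its notes call the research measurement strictly timed. Table 3 mentions research sessions. On this reading, care-report questions sit in the TAP-App and trial surveys in REDCap, and additional files not shown may say so. That stands as a reason to think volunteer collection may be limited, and it is why the point concerns what the text permits. It does not remove the point. The sentence under the outcome heading names an arm-specific channel as an outcome source, which is a statement in the plan and not a missing detail.

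A reader might infer more in three ways, none of them supported:

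- That the primary outcome is affected, or that the Discussion contradicts itself when it says the same process is used in both groups. That statement concerns GAS, which Table 2 describes as coming from a structured interview. It is simply not extended to the surveys.
- That baseline scores are contaminated by post-allocation volunteer visits. Nothing places a T0 outcome at such a visit.
- That the 13%, 39% and 71% rates describe the trial. They need the whole intervention arm to be surveyed by volunteers, and they ignore the Bonferroni rule for secondary analyses.

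**Conclusion.** The point holds for the secondary self-report outcomes up to T6 and for the EQ-5D-5L utilities. The text allows collection through unblinded intervention volunteers, does not require the same route in both arms, and gives controls no access to that route before the main comparison. The extent is unknown: it depends on how many surveys would go through volunteers and on a mode effect that the article does not give. Bonferroni lowers the false-positive rates but leaves the biased estimate and its confidence interval misplaced. The GAS score and the sample size are untouched, and the risk is weaker at 12 months. The wording should be changed; this does not threaten the primary result.

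**What to change.** Amend Client outcome measures to state that:

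1. every Table 2 self-report outcome compared between arms is collected at T0, T6 and T12 by the same mode in both arms (research staff using REDCap, or self-completion), within the research sessions already planned;
2. T0 is completed before allocation is disclosed;
3. TAP-App answers are used only for the care report and the process evaluation, not as trial outcomes.

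The cost is a wording change and some duplicate questions for intervention clients. No visits are added, because research follow-up at baseline, 6 and 12 months is already planned for both arms.
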